**Analysis::**

The individual components of the RE-AIM framework will be computed as percentages. A composite threshold of 80% will be deemed success. The secondary outcome variables will be compared to the pre-implementation period.

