### Primary outcome

The primary outcome will be implementation success, which will be assessed using three components of the RE-AIM framework (Fidelity, Reach, and Adoption). For each component of the framework, a threshold of 80% compliance across all three components will be considered success. This threshold is based on similar thresholds used in other studies and the understanding that, for policy implementation to have a meaningful impact on clinical outcomes and be sustainable as a long-term practice change, its adoption should be achieved in the greatest number of eligible patients as possible.^(33)^

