#### Primary outcome

The individual components of Reach, Fidelity, and Adoption of the RE-AIM framework will be computed as percentages, as shown in table 1. To assess fidelity, a checklist of key clinical interventions will be developed from the protocol and compared to the care delivered. This will include the frequency of blood pressure monitoring, the threshold for administering intravenous antihypertensives, and the timeliness of magnesium sulfate administration. Fidelity, reach, and adoption will be equally weighted, so a composite computation will be done using the mean. A threshold of 80% in each of the three domains will define success.

**Table 1 t1:** Primary and secondary outcome variables

Outcome	Measure and reporting
Implementation (primary outcome)	Fidelity: proportion of patients who are correctly managed with the protocol Numerator: number of patients who are correctly managed with the protocol Denominator: number of patients diagnosed with pre-eclampsia with severe features and eclampsia
	Reach: the proportion of patients who get managed with the protocol Numerator: number of patients who get managed with the protocol Denominator: number of obstetric emergency patients who presented at the Emergency Unit with the diagnosis of pre-eclampsia with severe features and eclampsia
	Adoption: proportion of patients who get managed with the protocol 6 months after the implementation Numerator: number of patients who get who get managed with the protocol in the 6th month of implementation Denominator: number of eligible patients who present to the Emergency Unit
Intervention effect and patient safety (secondary outcomes)	**Maternal** Hospital length of stay (in days) ICU referral and admission (expressed as a %) Hospital mortality (expressed as a %) ICU mortality (expressed as a %) Time to antihypertensive administration (in minutes; defined as the time between admission at the Emergency Department and the time of first administration of antihypertensive) Time to intravenous antihypertensive administration (in minutes; defined as the time between the first recorded blood pressure ≥ 180/110mmHg and the time of first administration of intravenous antihypertensive) Daily volume of fluid administration (expressed in mL/day) Time to magnesium sulphate administration (in minutes; defined as the time between admission at the Emergency Department and the time of first administration of magnesium sulphate)

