#### Secondary outcomes

The secondary outcome variables will be measured in the pre-implementation, peri-implementation, and post-implementation periods. The details of the outcome variables have been listed in table 1. Changes in measure (i.e., time, therapy, event rate) will be reported descriptively. The study is not powered to detect a significant change associated with the intervention; rather, these clinical process and outcome measures will provide a signal for safety and provide important feasibility information to inform future scalable studies if the protocol and co-design approach to implementation is found to be effective.

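### The abstract puts the 80% success cut on a composite (the mean of Fidelity, Reach and Adoption), while the Methods require 80% in each, so a result can pass the abstract's rule and fail the Methods' rule

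*Protocol article*

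**What the plan says.** The success criterion for the primary outcome appears in three places in the protocol article.

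- **Abstract, Analysis:** "A composite threshold of 80% will be deemed success". The cut is applied to one combined number.
- **Methods, Primary outcome:** "For each component of the framework, a threshold of 80% compliance across all three components will be considered success". The wording is loose, but it reads most naturally as a requirement on every component.
- **Analysis plan, Primary outcome:** "Fidelity, reach, and adoption will be equally weighted, so a composite computation will be done using the mean". The next sentence is "A threshold of 80% in each of the three domains will define success". The first of these gives the formula for the composite and attaches no threshold to it. The second puts the threshold on each domain.

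No sentence says how the abstract's rule relates to the one in the Methods, or what the composite is for once every domain has to reach 80%.

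**The concern.** A mean allows a strong domain to make up for a weak one; a requirement on each domain does not. The abstract's rule is therefore the more lenient.

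The components in Table 1 make compensation a practical possibility. Reach and Adoption both measure coverage, the second in month 6, and only Fidelity measures whether care followed the protocol correctly. Under the mean, two high coverage figures can hide poor correctness of care.

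The primary conclusion is a yes-or-no declaration of implementation success. If the text supports two rules, the choice between them could be made after the percentages are known.

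**Working it through.** **Inputs from the protocol**

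- Rule A (abstract, with the composite formula from the analysis plan): (F + R + A)/3 ≥ 80, where F, R and A are Fidelity, Reach and Adoption in percent.
- Rule B (analysis plan, and the natural reading of the outcome definition): F ≥ 80 and R ≥ 80 and A ≥ 80.
- Table 1 numerators: Fidelity, "Numerator: number of patients who are correctly managed with the protocol"; Reach, "Numerator: number of patients who get managed with the protocol"; Adoption, patients "managed with the protocol in the 6th month of implementation". Correctly managed patients are a subset of managed patients. Taking the Fidelity and Reach denominators as in effect the same patients, F ≤ R.
- No sample size, alpha or power is given for the primary outcome, so there is no planning figure to reproduce. The only statement on power, "The study is not powered to detect a significant change associated with the intervention", is about the secondary outcomes.

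**Step 1: direction of the conflict**

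If the smallest of F, R and A is at least 80, their mean is at least 80, so B implies A. The converse is false. The only possible disagreement is a pass on the mean with at least one domain below 80%.

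**Step 2: examples**

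| Reach | Fidelity | Adoption | Mean | Rule A | Rule B |
|---|---|---|---|---|---|
| 95 | 60 | 90 | 245/3 = 81.7 | success | failure |
| 90 | 70 | 80 | 240/3 = 80.0 | success | failure |
| 100 | 40 | 100 | 240/3 = 80.0 | success | failure |
| 100 | 39 | 100 | 239/3 = 79.7 | failure | failure |
| 90 | 85 | 82 | 257/3 = 85.7 | success | success |

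The lowest value a single domain can take while the mean still passes is 3 × 80 − 2 × 100 = 40%.

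**Step 3: how often the rules would disagree**

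The protocol gives neither patient numbers nor expected rates, so everything here is assumed: 100 patients for Reach and Fidelity and 20 for Adoption. Reach is binomial(100, r). Fidelity is binomial among those reached, with probability f/r, over the same 100. Adoption is binomial(20, a), drawn independently. Rules were applied to integer counts, so that results exactly at 80% are classified correctly: A is F + R + 5 × (Adoption count) ≥ 240; B is F ≥ 80, R ≥ 80 and Adoption count ≥ 16.

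| True Reach / Fidelity / Adoption (%) | P(success), mean | P(success), each domain | Disagreement |
|---|---|---|---|
| 95 / 90 / 90 | 100.0% | 95.6% | 4% |
| 90 / 85 / 85 | 97.2% | 77.5% | 20% |
| 90 / 76.5 / 85 | 87.5% | 20.1% | 67% |
| 75 / 64 / 75 | 2.1% | under 0.1% | 2% |

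In the third row 85% of managed patients are managed correctly, so true Fidelity is 0.90 × 0.85 = 76.5%, already below the cut. Observed Fidelity alone reaches 80% in only about 24% of those runs, which accounts for most of the gap.

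**The case against.** The strongest reply is that the Methods are not ambiguous. The analysis plan says what defines success, and the outcome definition points the same way. A mean can be computed as a summary beside an each-domain criterion without contradiction. On this view the error is one compressed sentence in the abstract. In addition, the three percentages are to be computed individually, so if they are reported a reader could see a failing domain.

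Much of this stands. A reader might infer that the analysis plan itself contains two competing rules. It does not, because it puts no threshold on the mean; the mean-based rule arises only when the abstract is read with the analysis plan's formula. Nor is the choice evenly balanced, since both Methods sections favour each domain.

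A reader might also take the 67% as the expected rate of disagreement. The protocol does not support that. It belongs to one assumed scenario with true Fidelity below 80%, and the other three scenarios give 2% to 20%.

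What does not stand is that the matter can be left alone or left to a separate analysis plan. The abstract states a different criterion for the primary outcome, and the Methods supply a formula for its composite without saying what it is for. That is contradictory text, not a detail held over.

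**Conclusion.** The contradiction is real and concerns the decision rule for the primary outcome. The sentence out of line is in the abstract. The two rules differ in one direction only: the mean can declare success where the each-domain rule declares failure, never the reverse. A reader might infer that any result could be called either way; only results that pass the mean with a domain below 80% can.

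The existence of the conflict rests on arithmetic alone. Its likely frequency rests on assumed patient numbers and rates. It is small when all domains are well above or well below 80%, and large when Fidelity sits just under the cut with high Reach. It should be corrected before the outcome percentages are known, because it can reverse the primary conclusion and costs almost nothing to repair.

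**What to change.** State one rule in the same words in the abstract, the Methods section on the primary outcome, and the analysis plan: implementation is a success only if Fidelity, Reach and Adoption are each at least 80%. This keeps the rule that the Methods already favour.

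- **Abstract:** replace the sentence on the composite threshold with this rule.
- **Methods, Primary outcome:** remove the phrase that could be read as pooling across components.
- **Analysis plan:** say that the equally weighted mean is a descriptive summary with no threshold, reported beside the three separate percentages.

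The cost is a few sentences of wording; design, data collection and component definitions are unaffected. The downside is that success is harder to claim than under the mean, by the amounts in the table above under the assumptions stated there.

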### Objectives

First, this study will assess the feasibility and impact of implementing a clinician-co-designed and context-adapted protocol for managing patients with pre-eclampsia and eclampsia.

Secondly, the study aims to evaluate the potential impact of the protocol on clinical care processes and outcomes (including safety endpoints).

The study will identify barriers and facilitators to implementing a clinician-co-designed protocol for managing pre-eclampsia with severe features and eclampsia, as reported by healthcare professionals (doctors, Nurses/Midwives, and pharmacists), and report adaptations to the protocol design and implementation strategy to overcome these barriers. To achieve these aims, the study combines Medical Research Council (MRC) recommended guidance for stakeholder-led protocol development, with an implementation evaluation tool, the Reach, Effectiveness -Adoption Implementation and Maintenance (RE-AIM) framework.^(12)^

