This study will generate new information regarding the effect of these strategies in the emergency, obstetrics, and maternal care population, drawing on perceptions and experiences from a diverse healthcare team. carefully designed with active stakeholder participation to overcome known barriers in implementation science. Stakeholder engagement before implementing a protocol enable the identification of context-specific barriers and givefosters clinicians’ sense of ownership, which improves the chances of success.^(23)^ Some Doctors and Nurses will be identified as champions to leverage their influence in the department to enhance implementation as documented in literatutre.^(31)^ Throughout the implementation period, progress will be audited periodically through data analysis to provide feedback to clinicians, as audit and feedback positively influence clinicians’ attitudes towards the implementation.^(2)^ The strategies to enhance implementation (education, stakeholder engagements, use of champions, audit, and feedback) will be employed over six weeks of active implementation. Their eventual withdrawal may pose a challenge to sustainability, but it is expected that the potential benefits in clinical outcomes and systems improvement would drive sustainability.

The success of these implementation strategies will be evaluated using the RE-AIM framework's 3 domains (fidelity, reach, and adoption). The RE-AIM framework is an effective tool for systematically evaluating healthcare interventions.^(32)^

Despite this study's purposeful selection of strategies to support context adaptation and engagement from clinical stakeholders, there is no assurance of success. The findings of the study will determine the ease of adoption and implementation of this clinical protocol, identify barriers and facilitators of the implementation process, and assess the impact on maternal outcomes specific to both the hospital and potentially relevant to the wider Ghanaian healthcare system. Though a single-center study, the findings may still serve as a guide for future policy implementation on a broader scale.

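### The Adoption component of the primary outcome is the Reach ratio measured again in month 6: it shows sustained reach and is mislabelled as a separate domain

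*Protocol article*

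**What the plan says.** The primary outcome is implementation success, judged on Fidelity, Reach and Adoption. Table 1 fixes the ratios:

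- Reach: "Reach: the proportion of patients who get managed with the protocol Numerator: number of patients who get managed with the protocol", with "Denominator: number of obstetric emergency patients who presented at the Emergency Unit with the diagnosis of pre-eclampsia with severe features and eclampsia".
- Adoption: "Adoption: proportion of patients who get managed with the protocol 6 months after the implementation". Its numerator counts patients "managed with the protocol in the 6th month of implementation", with "Denominator: number of eligible patients who present to the Emergency Unit".

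The framework is introduced under Objectives as "the Reach, Effectiveness -Adoption Implementation and Maintenance (RE-AIM) framework", so Maintenance is a dimension of its own. It is not one of the three that are assessed.

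Under Analysis plan, Primary outcome, the three components have equal weight and are averaged, and success requires 80% in each. The Primary outcome section under Evaluation also applies the 80% to all three. The Abstract instead sets the 80% threshold on the composite.

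Study timeline gives six weeks of active implementation, after which the research team withdraws to data collection only. The Discussion says that the strategies run for those six weeks and that their withdrawal may threaten sustainability. It also states: "The findings of the study will determine the ease of adoption and implementation of this clinical protocol".

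**The concern.** A primary outcome reported as success in three domains should rest on three distinct things. Here the second and third are the same kind of patient proportion, and the third is taken when the supporting strategies are no longer running. A result of at least 80% on that ratio would show that coverage lasted. It would be reported as Adoption, while the framework dimension that it fits, Maintenance, goes unnamed.

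Three things are at stake: what the primary conclusion may claim, how much weight one type of ratio has in the composite, and whether the same women enter two of the three components. The Discussion's statement on ease of adoption could also be read as resting on a ratio that does not address it.

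**Working it through.** The article states no expected rate or sample size on this point, so there is no figure to reproduce. The check compares the definitions and then works through the stated composite.

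**1. Definitions side by side (Table 1)**

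| | Reach | Adoption |
|---|---|---|
| Unit | patient | patient |
| Event | managed with the protocol | managed with the protocol |
| Eligible group | severe pre-eclampsia or eclampsia at the Emergency Unit | eligible patients at the Emergency Unit |
| Time | not stated | month 6 |

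Only the time differs. The Adoption row does not limit its denominator to month 6. That is a separate matter; here the denominator is taken as limited to that month. The row also gives two time points, 6 months after implementation and the sixth month of implementation. On either reading, the ratio is taken after the six active weeks.

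**2. Weight in the composite**

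C = (Fidelity + Reach + Adoption)/3. The ratio of patients managed to patients eligible carries 1/3 + 1/3 = 2/3 of the weight, and Fidelity carries 1/3.

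**3. Effect under the composite rule (assumed rates)**

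If coverage is the same at both times (Reach = Adoption = R), then C = (F + 2R)/3.

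- F = 60%, R = 90%: C = (60 + 90 + 90)/3 = 80.0%, which meets the threshold.
- Ratio counted once: (60 + 90)/2 = 75.0%, which does not.

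The Fidelity needed for a composite of 80% is 240 − 2R with three parts, and 160 − R if the ratio is counted once (all in %):

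| R | Three parts | Counted once |
|---|---|---|
| 85% | 70% | 75% |
| 90% | 60% | 70% |
| 95% | 50% | 65% |
| 100% | 40% | 60% |

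**4. Effect under the rule of 80% in each**

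F = 60% fails whatever R is. The second use of the ratio cannot compensate for a low component; it adds a hurdle. What remains wrong is the name of the domain that was passed.

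**5. Possible overlap of patients**

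Suppose that Reach covers months 1 to 6 with equal monthly numbers (an assumption, since no window is given). Each month then has 1/6 of the Reach weight, 1/3 × 1/6 = 1/18 = 5.6% of the composite. Month 6 also carries the whole of Adoption: 1/3 + 1/18 = 7/18 = 38.9%. That is seven times the coverage weight of any earlier month.

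**The case against.** Four objections deserve an answer.

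*The two ratios are not one quantity.* This stands. A reader might infer that Adoption only repeats Reach, but the strategies stop after six weeks and coverage may fall. With assumed values of 80% for Fidelity, 90% for Reach and 70% for Adoption, the later ratio fails its own threshold although Reach passes. The month-6 figure is worth having. The objection is to its name and to counting it as a different domain.

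*The double weight does no harm under the Methods rule.* This also stands. The 2/3 weight can change the result only under the Abstract's composite threshold. Which of the two rules governs is a separate question.

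*Double counting of patients is not established.* Correct. A reader might take it as fact that month-6 women enter both ratios. Table 1 does not exclude them from Reach, but it gives no Reach window either, so overlap is possible and not certain.

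*Adoption need not mean uptake by clinicians.* A reader might infer that the plan omits a required clinician-level measure, because training, feedback and champions all act on staff. The documents do not support that. No section defines adoption at clinician level, and the rationale for the threshold, under Primary outcome, speaks of adoption among eligible patients. The Discussion claims only to determine the ease of adoption. Interviews with ten clinicians before and after implementation, analysed for barriers and facilitators, can address this. A patient-level measure may therefore be deliberate. It still does not separate Adoption from Reach, and the same rationale refers to sustainable long-term practice change, which again points to Maintenance.

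**Conclusion.** The point holds as a mislabelled primary component. By Table 1's own definitions, Adoption is Reach taken in month 6, after active support has ended, and so measures sustained reach. This follows from the text and needs no assumption beyond limiting the denominator to that month.

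Its numerical size depends on the success rule. Under the composite rule, one type of ratio has 2/3 of the weight and can lift a Fidelity of 60% to a mean of 80.0%, given the assumed 90% at both times. Under the rule of 80% in each component, no low component is offset and only the claim is affected: a separate Adoption domain would be declared successful without having been measured. Patient overlap, and the sevenfold coverage weight of month 6, depend on a Reach window that the article does not state. The data remain usable; what needs correcting is what the primary outcome is said to show.

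**What to change.** 1. In Table 1 and wherever the three components are named, rename the month-6 ratio 'Maintenance (sustained reach)'.
2. State the window of each ratio, and compute Reach on patients presenting before month 6 so that no patient enters both.
3. Word the primary conclusion as fidelity, reach and sustained reach.
4. In the Discussion, rest the statement on ease of adoption on the interview analysis and not on this ratio.

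These are changes of wording and of one computation window, and they need no new data.

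Optionally, a clinician-level uptake proportion could be added as a descriptive measure. Its denominator would have to be defined one way throughout, either all trained staff or only those who saw an eligible patient. It would also have to allow for several staff caring for one woman, so a single treating-clinician field may not be enough. If wanted, it should be settled before the e-CRF is built and piloted.

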### Study participants

The study will include all patients who present at the obstetric emergency with the clinical assessment of pre-eclampsia with severe features or eclampsia. Severe features are defined as the presence of one of the following; platelets, 100 x 109, severe persistent right upper quadrant pain, renal insufficiency (serum creatinine > 1.1mg/dL or doubling of serum creatinine in the absence of renal disease), pulmonary oedema, visual disturbance, unexplained new-onset headache unresponsive to medication and HELLP syndrome acronym from hemolysis, elevated liver enzymes and low platelets.^(13)^

Patients who present dead on arrival to the emergency unit will be excluded. There are a few patients who will not present to the ED with pre-eclampsia/eclampsia but may develop the condition days later during a hospital admission for another pregnancy-related condition. These patients will also be excluded, given the variation in their hospital journey and the likely limited number of affected patients.

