### Analysis plan

#### Patient demographics and patient characteristics

Descriptive statistics (mean/median) will be used to describe baseline patient characteristics: age, gravidity, parity, and blood pressure. The patient categories of antepartum and postpartum will be reported as percentages. The presenting diagnoses of the patients will also be reported as percentages.

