	**Fetal** Neonatal ICU admission (expressed as a %) [Numerator = number of babies admitted to neonatal ICU, denominator = number of babies delivered] Preterm birth (expressed as a %) [Numerator = number of preterm deliveries, denominator = number of babies delivered] Placental abruption (expressed as a %) [Numerator = number of placental abruption, denominator = number of babies delivered] IUFD (expressed as a %) [Numerator = number of preterm intrauterine fetal deaths, denominator = number of babies delivered] IUGR (expressed as a %) [Numerator = number of IUGR, denominator = number of babies delivered] Average Apgar score at 1 and 5 minutes

ICU - intensive care unit; IUFD - intrauterine fetal death; IUGR - intrauterine growth restriction.

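### The neonatal ICU admission rate in Table 1 counts stillborn babies in its denominator, so more fetal deaths lower it; live births are the right base, and fetal outcomes should be split by status at arrival.

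*Protocol article*

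**What the plan says.** In the protocol article, Table 1 (fetal outcomes) gives five percentages, all on the same base:

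- Neonatal ICU admission: "Numerator = number of babies admitted to neonatal ICU, denominator = number of babies delivered".
- Preterm birth: "Numerator = number of preterm deliveries, denominator = number of babies delivered".
- Placental abruption: "Numerator = number of placental abruption, denominator = number of babies delivered".
- IUFD: "Numerator = number of preterm intrauterine fetal deaths, denominator = number of babies delivered".
- IUGR: "Numerator = number of IUGR, denominator = number of babies delivered".

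Apgar score is listed as an average at 1 and 5 minutes, with no statement of which babies enter it. The article does not define a baby delivered, either by live birth or by when the birth took place relative to the mother's arrival.

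On who is in the cohort, Study participants says "The study will include all patients who present at the obstetric emergency with the clinical assessment of pre-eclampsia with severe features or eclampsia". The exclusions there are "Patients who present dead on arrival to the emergency unit will be excluded" and women who develop the condition later, during an admission for another reason. Women who have already given birth are not excluded. Patient demographics and patient characteristics confirms that they are expected: "The patient categories of antepartum and postpartum will be reported as percentages".

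The Secondary outcomes part of the analysis plan has these measures taken before, during and after implementation and reported descriptively. It says the study is not powered for them and gives their purpose as a safety signal and feasibility information. The Abstract names the pre-implementation period as the comparator.

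**The concern.** A rate should be taken over those who can have the event. A stillborn baby cannot be admitted to neonatal ICU, so leaving it in the denominator makes the rate a product of two things: how often live-born babies are admitted, and how many babies are born alive. The second factor works in the wrong direction for a safety measure. More fetal deaths look like fewer admissions, and fewer deaths look like more.

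The second issue is case mix. For a woman who arrives after delivery, her baby's preterm birth, abruption, IUFD, IUGR and Apgar score were settled before the unit's protocol could act. If such babies are counted, they dilute any real change. They can also move the rates between periods when the share of postpartum arrivals changes. With no concurrent control and only a descriptive before-after comparison, the definition of the rate carries much of the interpretation.

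**Working it through.** The article states no fetal event rate, stillborn share or postpartum share, so there is no figure of its own to reproduce. Every rate below is an assumption chosen to show direction and scale.

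**Step 1. Are stillborn babies in the denominator?** The IUFD row divides fetal deaths by the same base. A percentage needs its numerator to lie within its denominator, so that base includes babies born dead. The neonatal ICU row uses the identical phrase.

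**Step 2. Effect on the neonatal ICU rate.** Let *a* be admissions per live birth and *s* the stillborn share of all births.

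Tabulated rate = *a* × (1 − *s*)

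| Assumed *a* | *s* = 5% | *s* = 15% | Shift |
|---|---|---|---|
| 20% | 0.20 × 0.95 = 19.0% | 0.20 × 0.85 = 17.0% | 2 points |
| 40% | 0.40 × 0.95 = 38.0% | 0.40 × 0.85 = 34.0% | 4 points |
| 50% | 0.50 × 0.95 = 47.5% | 0.50 × 0.85 = 42.5% | 5 points |

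Admission per live birth is constant within each row. Read from right to left, a fall in stillbirth from 15% to 5% raises the 40% row from 34% to 38%, so an improvement would look like harm. On a live-birth base the rate stays at *a* throughout.

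**Step 3. Effect of postpartum arrivals, if their babies are counted.** Let *p* be the share of babies born before arrival.

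Overall rate = (1 − *p*) × rate after arrival + *p* × rate before arrival

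- Neonatal ICU, assumed 40% after and 10% before: *p* = 10% gives 0.36 + 0.01 = 37%; *p* = 30% gives 0.28 + 0.03 = 31%.
- IUFD, assumed 12% after and 3% before: *p* = 10% gives 0.108 + 0.003 = 11.1%; *p* = 30% gives 0.084 + 0.009 = 9.3%.
- If the two groups have equal rates, the shift is zero for any *p*.
- Dilution: if before-arrival rates do not change, a true 10-point change in the other babies appears as 10 × (1 − 0.2) = 8 points at *p* = 20%, and 10 × (1 − 0.4) = 6 points at *p* = 40%.

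**Step 4. Price of using only women undelivered at arrival.** Interval width grows by 1/√(1 − *p*): 1/√0.8 = 1.12 at 20% and 1/√0.6 = 1.29 at 40%, or about 12% to 29% wider.

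**The case against.** The strongest reply is that little can be hidden. IUFD is reported alongside on the same base, and Secondary outcome in the Methods also lists fetal mortality. In the example, a 10-point rise in stillbirth would stand out beside a 4-point fall in admissions, and a reader could recover the live-birth rate by division: 0.34 / 0.85 = 0.40. Most of this stands and limits the seriousness. The recovery is incomplete, though, because the IUFD numerator in Table 1 counts only preterm deaths, so one minus the IUFD rate need not be the live-born share.

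A reader might infer more than the article supports:

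- **That all five fetal rates have the wrong base because of stillbirths.** They do not. All births is the right base for IUFD and acceptable for preterm birth, abruption and IUGR.
- **That the stillbirth effect is unrelated to the protocol.** Fetal death is something the protocol may influence. It is a competing outcome for neonatal ICU admission, not mere noise.
- **That babies born before arrival are certainly counted.** This is inferred from open eligibility and an undefined term. The term could mean babies delivered during the study admission.
- **That a change in postpartum share moves every fetal rate.** It does so only where the rate differs between the groups, and the article gives no such rates.
- **That twins bias the preterm and abruption rates.** This assumes one count per mother, which the table does not say.

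It is also fair to say that a condensed article may leave finer definitions to a fuller document. That answers the undefined term, but not the neonatal ICU row, where the rule is printed.

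**Conclusion.** The point holds for neonatal ICU admission: the stated denominator includes babies who cannot have the event, and the resulting rate moves the wrong way when fetal deaths change. Under assumed admission of 20% to 50% of live births and stillbirth of 5% versus 15%, the distortion is 2 to 5 points. The actual size cannot be determined from the article.

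The postpartum issue is secondary and conditional. Nothing limits the denominator to births after arrival, so a split by status at arrival is warranted, but whether and how far the rates shift depends on shares and rates that are not given.

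The effect is confined to secondary, descriptive, unpowered outcomes. The primary outcome (fidelity, reach and adoption) is untouched. A correction is still worthwhile, because these rates are meant to serve as a safety signal and the bias does not shrink with more patients.

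**What to change.** 1. In Table 1, use live births as the denominator for neonatal ICU admission, and state that average Apgar score is taken over live births.
2. Keep all births as the denominator for IUFD and IUGR, and present neonatal ICU admission next to IUFD so that the two are read together.
3. State whether births before the mother's arrival are counted. Show fetal outcomes split by antepartum or postpartum status at arrival, a category the analysis plan already reports, and name women undelivered at arrival as the group for the before-after safety comparison. Show babies of postpartum arrivals separately rather than dropping them.

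The first two changes cost a few words in the table and a live-birth indicator for each baby in the electronic case report form, which the article says is still to be developed. The third costs precision in the comparison group, in proportion to the postpartum share. The article does not give that share; an assumed 20% to 40% would widen intervals by about 12% to 29%, which is not trivial. No extra recruitment is needed.
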